#### **8.4 Day 10 evaluation and treatment procedures**

- 8.4.1 Record concomitant medications on the CRF.
- 8.4.2 Perform a complete physical examination (study doctor).
- 8.4.3 Assess vital signs prior to treatment application.
- 8.4.4 Assess the active cutaneous lesions identified during the screening/baseline visit. Note presence and description of any additional lesions that may have appeared since previous visit. Stop therapy if a mucosal lesion has developed
- 8.4.5 Record adverse events occurring since the last evaluation.
- 8.4.6 Take a drawing of each lesion using a plastic sheet, drawing the borders of each lesion.
- 8.4.7 Obtain photograph of the representative cutaneous lesion first photographed at baseline following the same procedures of section 8.2.7
- 8.4.8 Collect blood for safety evaluations as follows (study technician):  
Approximately 2.5 ml anticoagulated (EDTA) whole blood for CBC, white cell differential and platelet count.  
  
Approximately 8.5 ml whole blood into serum separator tube (SST) for serum chemistry testing. Chemistries to include: ALT, AST, total bilirubin, alkaline phosphatase, pancreatic amylase, glucose and creatinine.
- 8.4.9 Electrocardiogram: Only if a cardiovascular condition should be monitored.

- 8.4.10 Administer treatment to the patient as described in Section 7 as long as there are no severe adverse events as detailed in section 10.1 .

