#### 4.2 Exclusion Criteria

Patients must have NONE of the following criteria to be eligible for inclusion into the study:

- a) Having a lesion(s)  $> 25 \text{ cm}^2$
- b) More than 6 cutaneous lesions.
- c) Have a mucosal lesion.
- d) History of previous exposure to imiquimod or anti-*Leishmania* treatment.
- d) Participation in another experimental protocol and/or have received investigational products within 30 days prior to study entry.
- e) History of any acute or chronic illness (other than CL) or medication that, in the opinion of the investigators, may interfere with the evaluation of the trial (i.e History of heart illness, corticotherapy)
- f) History of significant psychiatric illness.
- g) History of previous anaphylaxis or severe allergic reaction to one or more of the proposed drugs.
- h) Patients who are unlikely to cooperate with the requirements of the study protocol.
- i) Concomitant infection (ex. Bartonellosis, Sporotrichosis, Mycobacteria)
- j) Women who are pregnant or breast feeding.

..

These inclusion and exclusion criteria were established in order to provide the optimal opportunity for treatment response.

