## 8.2 Baseline (Day 1): Evaluation and treatment procedures.

Patients who meet all inclusion/exclusion criteria at the screening visit will be asked to return to the clinic for the baseline visit (Day 1). Upon arrival, the following evaluations will be completed and recorded on the CRF by the study doctor:

- 8.2.1 Study I.D. number will be assigned by the pharmacist to the patient and placed on the CFR and consent form by the study doctor at each site .
- 8.2.2 Vital signs assessment. Patients with abnormal pulse rate, blood pressure or oral temperature  $>38^{\circ}\text{C}$  ( $100.4^{\circ}\text{F}$ ) or having acute illness on the day of the therapy must NOT receive the therapy. Temperature and acute illness must resolve within 7 days of initial scheduled visit in order to proceed with the study.
- 8.2.3 Limited physical exam, noting any changes from the screening examination. This must include any changes in the cutaneous lesion description obtained during the screening visit. Note: Do NOT proceed if patient has developed a mucosal lesion.
- 8.2.4 Female patients of childbearing potential must have a documented negative urine pregnancy test on day 1 of therapy and the date of the last menstrual period recorded.
- 8.2.5 Record any concomitant medications.

8.2.6 Make a drawing of each lesion using a plastic sheet, drawing the borders of each lesion on Day 1, and place in the CRF.

8.2.7 Photograph all cutaneous lesions using a digital camera with daylight (no flash) and with a distance of 15 cm from the center of lesions. A standard rule with a label of the ID patient code and date will be placed beside the lesion before taking the photograph. The pictures will be stored in a computer at IMTAvH sites and they will be accessed only by the study team.

Upon completion of these evaluations, the study doctor will review the inclusion/exclusion criteria for each patient. Patients who meet all eligibility criteria will have the following additional procedures completed on Day 1:

8.2.8 Provide the treatment (study nurse) as described in Section 7.

8.2.9 Monitor adverse events and cream application site reactions for 30 minutes post treatment and document on the CRF.

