### **8.3 Days 2-9 evaluation and treatment procedures**

8.3.1 Record any concomitant medications on the CRF.

8.3.2 Perform limited physical examination (study doctor).

8.3.3 Assess vital signs prior to treatment application.

8.3.4 Assess the active cutaneous lesions identified during the screening/baseline visits. Note presence and description of any additional lesions or mucosal lesions that may have appeared since the previous visit.

8.3.5 The study nurse will administer the treatment to the patient as described in Section 7 as long as there are no severe adverse events as detailed in section 10.1.

- 8.3.6 Monitor adverse events and injection site reactions for 30 minutes post treatment and document on the CRF.

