**8.5 Days 11-19 evaluation and treatment procedures**

- 8.5.1 Record any concomitant medications.
- 8.5.2 Perform limited physical examination.
- 8.5.3 Assess vital signs prior to treatment application.
- 8.5.4 Assess the active cutaneous lesions identified during the screening/baseline visit. Note presence and description of any additional lesions or mucosal lesions that may have appeared since previous visit.
- 8.5.5 Administer treatment to the patient as described in Section 7 as long as there are no severe adverse events as detailed in section 10.1.
- 8.5.6 Monitor adverse events and injection site reactions for 30 minutes post treatment and document on the CRF.

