**8.6 Day 20 (Last day of treatment) evaluation and treatment procedures**

- 8.6.1 Record concomitant medications.
- 8.6.2 Perform a complete physical examination.
- 8.6.3 Assess the active cutaneous lesions identified during the screening/baseline visit. Note presence and description of any additional lesions that may have appeared since previous visit.
- 8.6.4 Record adverse events occurring since the last evaluation.
- 8.6.5 Obtain photograph of the representative cutaneous lesion first photographed at baseline following the same procedures of section 8.2.7
- 8.6.6 Collect blood for safety evaluations as follows:

Approximately 2.5 ml anticoagulated (EDTA) whole blood for CBC, white cell differential and platelet count.

Approximately 8.5 ml whole blood into serum separator tube (SST) for serum chemistry testing. Chemistries to include: ALT, AST, total bilirubin, alkaline phosphatase, pancreatic amylase and creatinine.

8.6.7 Electrocardiogram: Only if a cardiovascular condition should be monitored during the antimony therapy.

8.6.8 Administer treatment to the patient as described in Section 7 as long as there are no severe adverse events as detailed in section 10.1.

Patients will be evaluated during the follow up period by the study team as described in the section 9.

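### A mucosal lesion that appears during treatment triggers a stop instruction at Day 10 but on no other on-treatment day

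*Protocol*

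**What the plan says.** Section 8 of the protocol sets out the procedures visit by visit.

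- **Days 2-9 (8.3.4, 8.3.5).** The lesion check reads: "Note presence and description of any additional lesions or mucosal lesions that may have appeared since the previous visit". The nurse then treats "as long as there are no severe adverse events as detailed in section 10.1".
- **Day 10 (8.4.4, 8.4.10).** The lesion check ends with "Stop therapy if a mucosal lesion has developed". The dosing item later in the same visit is conditioned only on severe adverse events.
- **Days 11-19 (8.5.4, 8.5.5).** The check is again "Note presence and description of any additional lesions or mucosal lesions that may have appeared since previous visit", followed by "Administer treatment to the patient as described in Section 7 as long as there are no severe adverse events".
- **Day 20 (8.6.3, 8.6.8).** The check is "Note presence and description of any additional lesions that may have appeared since previous visit", with no word on mucosal lesions. Dosing carries the same severe-adverse-event condition.

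Before treatment, section 4.2 lists "Have a mucosal lesion" among the exclusions, and the Day 1 check in 8.2.3 says "Do NOT proceed if patient has developed a mucosal lesion".

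**The concern.** The protocol regards a mucosal lesion as important enough to exclude a patient at entry and to stop therapy at Day 10. Yet the visits either side of Day 10 name the same event and attach only a duty to record it. Followed as written, the day on which the lesion is seen decides whether there is an instruction to stop.

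This is first a matter of patient safety. It also means that patients with the same event can receive different amounts of treatment, and have different discontinuation records, for no reason other than the calendar.

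**Working it through.** There is no planned figure to reproduce. The check sets the visits side by side and then looks for a general rule that would reconcile them.

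| Treatment days | Number of days | Instruction on a mucosal lesion | Stated condition for dosing |
|---|---|---|---|
| 2-9 (8.3) | 8 | Note and describe | No severe adverse event |
| 10 (8.4) | 1 | Stop therapy (8.4.4) | No severe adverse event (8.4.10) |
| 11-19 (8.5) | 9 | Note and describe | No severe adverse event |
| 20 (8.6) | 1 | None | No severe adverse event |

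**Count.** The treatment days after Day 1 number 8 + 1 + 9 + 1 = 19. A stop instruction stands on 1 of them. On 8 + 9 = 17 days the lesion is to be noted and no stop is given. On 1 day it is not mentioned.

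**What the text yields for exposure.** Section 7.1 gives antimony once daily for 20 consecutive days. Assume that only the written instructions are applied, that no severe adverse event is declared, and that the Day 10 stop takes effect before that day's dose.

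- First seen on Day 9: dosed on Day 9, stopped at Day 10. Doses received: 9 (Days 1-9).
- First seen on Day 10: stopped at Day 10. Doses received: 9. If 8.4.10 is followed instead of 8.4.4, the Day 10 dose is also given, making 10.
- First seen on Day 11: no stop instruction. Doses received: up to 20, which is 20 - 9 = 11 more than a patient whose lesion was seen a day earlier.

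**Is there a general rule elsewhere?**

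- *Section 10.1.* The dosing items point here. Severity is graded by the investigator's judgment, and severe means that ordinary daily life is prevented. A new mucosal lesion need not meet that.
- *Section 11.* The doctor may choose to remove a patient who worsens beyond what is expected, and investigators may remove one for a severe adverse event, pregnancy or intercurrent illness. Mucosal lesions are not named, and removal is optional.
- *Section 9.1.* Mucosal lesions are recorded at follow-up. This does not bear on treatment days.

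None of these supplies a rule for all treatment days.

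**The case against.** The strongest reply is that this is an omission rather than a contradiction. No sentence tells staff to go on treating despite a mucosal lesion. The severe-adverse-event condition also stands in 8.4.10, beside the stop in 8.4.4, so the protocol does not use it as a complete list of reasons to withhold. That is fair. A reader might infer that the text orders treatment to continue on 17 days. It does not: it gives no stop instruction on those days. The inconsistency remains, because sections 8.3 and 8.5 name the event and ask only for a record, while 8.4 names it and asks for a stop.

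Second, the Day 10 wording looks back and comes with a complete physical examination, whereas Days 2-9 have limited ones. It can therefore catch a lesion that arose on Days 2-9. This narrows the gap, but such a lesion is caught only at Day 10, and a lesion first seen on Days 11-20 meets no later stop.

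Third, the adverse event definition includes marked deterioration of the study disease, and section 11 lets the doctor act on unexpected worsening. Both routes are open to a careful physician. Both are discretionary, so they reduce the practical risk without supplying a rule.

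Fourth, a reader might count the Day 1 bar as part of the conflict. It is not. It applies the entry exclusion before any dose, and an entry criterion may differ from an on-treatment rule without contradiction.

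**Conclusion.** The point holds for the on-treatment days: Day 10 against Days 2-9, 11-19 and 20, and item 8.4.4 against item 8.4.10 within Day 10. The wording should be corrected because it concerns a safety instruction. The exposure contrast above is what the written text permits if discretion is not used, not a forecast. The protocol gives no incidence of mucosal lesions over the 20 days, and the number affected is probably small.

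Two further inferences are not supported. A reader might conclude that the analysis of a stopped patient is left open and that section 15 needs an added line. Section 8.7 already classes a new lesion as failure, and section 15 already plans an intention-to-treat analysis of all randomized patients. Finer event handling is commonly left to a statistical analysis plan. A reader might also infer bias between arms or diverging practice between Lima and Cusco. Both sites work from the same text and the treating staff are blinded (section 6). Nothing in the protocol shows either effect.

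**What to change.** The investigators should reconcile sections 8.3, 8.4, 8.5 and 8.6 with one another and with section 11, so that one stated rule for a new mucosal lesion applies on every treatment day. Items 8.4.4 and 8.4.10 should be made to agree, for example by having each visit's dosing item refer to that rule. Which rule applies is for the investigators to decide.

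The cost is a protocol wording change, with the ethics board approval that section 16.4 requires for any modification. Sample size, visits and planned analyses are unaffected.

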**8.5 Days 11-19 evaluation and treatment procedures**

- 8.5.1 Record any concomitant medications.
- 8.5.2 Perform limited physical examination.
- 8.5.3 Assess vital signs prior to treatment application.
- 8.5.4 Assess the active cutaneous lesions identified during the screening/baseline visit. Note presence and description of any additional lesions or mucosal lesions that may have appeared since previous visit.
- 8.5.5 Administer treatment to the patient as described in Section 7 as long as there are no severe adverse events as detailed in section 10.1.
- 8.5.6 Monitor adverse events and injection site reactions for 30 minutes post treatment and document on the CRF.

**8.6 Day 20 (Last day of treatment) evaluation and treatment procedures**

- 8.6.1 Record concomitant medications.
- 8.6.2 Perform a complete physical examination.
- 8.6.3 Assess the active cutaneous lesions identified during the screening/baseline visit. Note presence and description of any additional lesions that may have appeared since previous visit.
- 8.6.4 Record adverse events occurring since the last evaluation.
- 8.6.5 Obtain photograph of the representative cutaneous lesion first photographed at baseline following the same procedures of section 8.2.7
- 8.6.6 Collect blood for safety evaluations as follows:

Approximately 2.5 ml anticoagulated (EDTA) whole blood for CBC, white cell differential and platelet count.

Approximately 8.5 ml whole blood into serum separator tube (SST) for serum chemistry testing. Chemistries to include: ALT, AST, total bilirubin, alkaline phosphatase, pancreatic amylase and creatinine.

8.6.7 Electrocardiogram: Only if a cardiovascular condition should be monitored during the antimony therapy.

8.6.8 Administer treatment to the patient as described in Section 7 as long as there are no severe adverse events as detailed in section 10.1.

Patients will be evaluated during the follow up period by the study team as described in the section 9.

#### **8.7 Analysis of the response to therapy at 1, 2, 3, 6, 9, 12 months of follow-up:**

Improvement: Significant reduction in the size of the lesion at the time of evaluation (Stages M1-M3) compared to baseline.

Cure: Complete re-epithelialization of the lesion without inflammation (Stage M4).

Failure: Any one of the following or combined options

Stage MO at 1 month of follow up after the treatment

Stage M1 at 3 months of follow up after the treatment

Regression of the clinical stage to a lower stage or development of a new lesion.

#### **8.8 Safety and tolerability evaluation**

**8.8.1 Grading of side effects of the treatment at the at the cream application site (pain, pruritus, erythema and swelling):**

Grade 0 = none

Grade 1 = mild (easily tolerated)

Grade 2 = moderate (sufficiently discomforting to interfere with daily activities)

Grade 3 = severe (prevents normal daily activity)

**8.8.2 Grading of pain at the site of application site** will be according to the following definitions:

None

Mild (Some pain but does not limit the movement of the place where the lesion is located.)

Moderate (Limits movement)

Severe (Cannot move the place where the lesion is located)

**8.8.3 Grading of pruritus (itching) at the cream application site** will be made according to the following definitions:

None

Mild (Noticeable but easily tolerated)

Moderate (Sufficiently discomforting to slightly interfere with daily activities)

Severe (Constant discomfort. Leads to restriction of normal daily activities)

**8.8.4 Grading of erythema (inflammation) at the cream application site** will be according to the following:

None (0 to <1 cm in diameter)

Mild (1 to 4 cm in diameter)

Moderate (5 to 9 cm in diameter)

Severe (10 cm or greater in diameter)

**8.8.5 Grading of swelling at the cream application site** will be according to the following:

None

Mild (Some tenderness)

Moderate (Limits movement of the place where the lesion is located)

Severe (Cannot move the place where the lesion is located)

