#### Assessment of Intensity/Severity

The assessment of intensity/severity will be based on the investigator's clinical judgment and categorized as follows:

**Mild:** An adverse event which is easily tolerated by the patient, causing minimal discomfort and not interfering with daily activities.

**Moderate:** An adverse event, which is sufficiently discomforting to interfere with normal daily activities.

**Severe:** An adverse event, which prevents normal daily activities.

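### Local-reaction scales in Protocol section 8.8: swelling is graded as pain, the erythema bands have gaps and no measurement rule, and no rule says which scale governs

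*Protocol*

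**What the plan says.** Section 8.8.1 sets one general scale, grades 0 to 3, for "pain, pruritus, erythema and swelling" at the application site. Its levels rest on daily activity, and the top level is "Grade 3 = severe (prevents normal daily activity"). Sections 8.8.2 to 8.8.5 then define each sign separately:

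- Erythema (8.8.4) is graded by diameter alone: none below 1 cm, mild from 1 to 4 cm, "Moderate (5 to 9 cm in diameter"), and severe from 10 cm upwards.
- Swelling (8.8.5) starts at "Mild (Some tenderness"); moderate means that movement of the site is limited, and severe that the site cannot be moved.

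Section 10.1 has its own severity categories for adverse events. Severe there is "An adverse event, which prevents normal daily activities". The daily treatment items (8.3.5, 8.4.10, 8.5.5 and 8.6.8) allow treatment "as long as there are no severe adverse events as detailed in section 10.1".

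Two other provisions bear on size. Section 4.2 excludes lesions above 25 cm², and section 7.2 has the cream applied to the whole lesion plus a 0.5 cm margin of normal skin.

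**The concern.** The cream is the only component that differs between the arms, so local reactions are the main tolerability comparison. If the swelling scale records pain, the trial will have two pain results and no swelling result. If a measured erythema has no grade, or has one grade under 8.8.1 and another under 8.8.4, the table of reactions depends on how each doctor at the two sites resolves the text. A later analysis plan cannot repair this, because the definitions decide what is written down at the visit. A grade not taken before the first application cannot be recovered as such.

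**Working it through.** No sample-size, power or event figure is involved, so there is no figure of the plan to reproduce. The check compares the definitions and then works through the geometry of the erythema bands.

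**1. Swelling against pain**

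| Level | Pain (8.8.2) | Swelling (8.8.5) |
|---|---|---|
| Mild | Some pain, movement not limited | Some tenderness |
| Moderate | Movement limited | Movement of the site limited |
| Severe | Site cannot be moved | Site cannot be moved (same wording) |

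No swelling level refers to size, extent or firmness. A site that is swollen but neither tender nor stiff fits no level above None. A tender site without swelling fits Mild. Movement is also a poor anchor for many facial sites, and sections 5 (item l) and 7.2 expect facial lesions.

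**2. Gaps in the erythema bands**

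The bands are 0 to <1, 1 to 4, 5 to 9, and ≥10 cm. Read as a continuous measurement, the intervals (4, 5) and (9, 10) have no grade. That is (1 + 1)/(10 − 1) = 2/9 = 22% of the range from 1 to 10 cm. Whole-centimetre readings would close the gaps, but the protocol does not ask for them, and the lowest cut (<1 cm) is written as a continuous one.

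**3. What the lesion itself would contribute, if the diameter includes it**

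The protocol does not say whether it does, so this step is conditional. Inputs: area limit 25 cm² (4.2) and margin 0.5 cm on each side (7.2). Assumption: round lesion, so d = 2√(A/π), and treated diameter = d + 1.0 cm.

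- A = 25 cm²: d = 5.64 cm, which is Moderate; with the margin 6.64 cm, also Moderate.
- d = 5 cm needs A = π·5²/4 = 19.63 cm². Round lesions from 19.63 to 25 cm² are therefore Moderate on their own footprint.
- d = 4 cm is A = π·4²/4 = 12.57 cm². Lesions between 12.57 and 19.63 cm² fall in the first gap. With the margin, 12.57 cm² reaches 4 + 1 = 5 cm, which is Moderate.
- d = 1 cm is A = π·1²/4 = 0.79 cm². A red lesion of this size or more is at least Mild before any cream.
- Severe (10 cm) needs π·10²/4 = 78.54 cm², or π·9²/4 = 63.62 cm² plus the margin. Both exceed 25 cm², so a round eligible lesion cannot reach Severe by itself.

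Shape matters at the extreme. For an ellipse with axis ratio r the long axis is 2√(25r/π). At r = 3 it is 9.77 cm, in the second gap, and 10.77 cm with the margin. The protocol does not say which axis the diameter is.

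If only redness beyond the lesion border is measured, none of step 3 applies.

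**4. Baseline**

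On Day 1 the lesion is described, traced and photographed (8.2.3, 8.2.6, 8.2.7). Application-site reactions are monitored only after treatment (8.2.9). No erythema or swelling grade is required before the first application.

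**5. Which scale governs**

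| Source | Basis for severe |
|---|---|
| 8.8.1, erythema and swelling | Daily activity prevented |
| 8.8.4, erythema | Diameter 10 cm or more |
| 8.8.5, swelling | Site cannot be moved |
| 10.1, any adverse event | Daily activity prevented |

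Erythema of 10 cm or more that leaves activity intact is Severe by 8.8.4 but not by 8.8.1 or 10.1. Section 8.8 has no precedence rule.

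**The case against.** The strongest reply is that this is drafting. Section 8.8.1 can be read as the general scale and 8.8.2 to 8.8.5 as its sign-specific definitions, with diameters read to the nearest centimetre. A diameter does measure the extent of erythema, and the pruritus scale broadly follows 8.8.1. No hypothesis or sample-size figure rests on these grades, and the Day 1 description, tracing and photograph give some baseline record. All of that is fair and limits the weight of the point. It does not rescue the swelling scale, which lacks any measure of swelling on every reading, and neither the precedence nor the rounding is written down.

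Three stronger readings are tempting, and the documents do not support them:

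- A reader might infer that the erythema diameter includes the lesion, and so that disease inflates the grades in both arms and dilutes the difference between them. The application site is the lesion plus a margin, which makes this a natural reading, but 8.8.4 is silent. The protocol gives no distribution of lesion sizes either, so no dilution can be quantified.
- A reader might infer a three-way conflict over the word severe. Sections 8.8.1 and 10.1 use the same anchor; only the sign-specific scales depart from it.
- A reader might infer that the decision to continue treatment depends on which section the doctor reads. The treatment items cite section 10.1 by number, so the condition has one definition. What is missing is a statement of how a Severe grade under 8.8 relates to it.

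**Conclusion.** Three defects hold on the text:

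- The swelling scale nearly duplicates the pain scale and records no extent of swelling.
- The erythema bands leave two 1 cm intervals ungraded, with no rule on rounding, on inclusion of the lesion or on a pre-application grade.
- 8.8.1 grades erythema and swelling on a different basis from 8.8.4 and 8.8.5, and nothing says which governs.

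The first and third need no assumption. The 22% figure assumes continuous readings. The lesion-footprint figures assume that the diameter includes the lesion and, except for the ellipse, that the lesion is round.

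The finding is minor. It affects how local tolerability is recorded and compared. It does not touch the cure endpoint, the sample size or the treatment condition defined through section 10.1.

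**What to change.** Reword section 8.8 and its CRF page:

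1. Grade swelling by a measure of swelling that is distinct from pain, tenderness and movement.
2. Make the erythema bands contiguous. State whether the lesion is included, which axis is measured and how readings are rounded.
3. Record erythema and swelling before the first application on Day 1, and report change from that grade.
4. Reconcile 8.8.1 with 8.8.2 to 8.8.5, and state how their levels relate to the severity definition in 10.1. Which severity threshold should govern treatment is a clinical decision for the investigators, and this review proposes none.

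The cost is a text revision, a revised CRF page and one extra assessment per patient on Day 1. The downside is slightly less comparability with earlier studies, if those used the present bands.
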